### Outcome measures

#### Primary outcome measure

Safety will be assessed comparing the rate of treatment related complications between groups (proportion of treatment related complications among groups) at 24 h and 3, 6, and 12 months from treatment administration, including those related with anesthetic procedure, IMP administration and those occurring after the procedure.

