### Statistical considerations

#### Sample size calculation

A formal size calculation based on the expected differences for the primary outcome has not been performed. This is a phase II, dose-finding study, and no previous data on the preliminary efficacy of Ad-MSC with CLI including type 2 DM patients are available to date. A sample size of 30 patients per group was deemed appropriated based on the possibility to reach normality and the feasibility to recruit 90 eligible patients in 10 university hospitals.

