#### Statistical analysis

Primary, secondary, and tertiary outcomes (safety, efficacy, and quality of life) will be assessed in intention to treat (ITT) and per protocol (PP) populations [39]. ITT population will include all patients who sign the informed consent and receive the investigational product. PP population will include patients who complete the 12-month follow-up period. A descriptive analysis of baseline characteristics of patients included in three groups will be performed. Quantitative variables will be expressed as mean and/or median and standard deviation and/or range. Qualitative variables will be expressed as percentages. When possible, the 95% confidence interval of each of the estimates made will be calculated. To analyze the primary outcomes, 24 h and 3, 6, and 12 months complication rates will be described and compared for the three groups using the Chi-square test or, if necessary, the Fisher exact test. The analyses of the secondary and tertiary outcomes will be performed as follows: qualitative variables will be described in terms of the percentage of improvement of the medical condition in each group and compared using the Chi-square test, or alternatively Fisher’s exact test. VAS scale, SF-12 scale, VascuQuol-6 scale, and the rest of the quantitative variables will be assessed by describing changes in variables at 3, 6, and 12 months from baseline, in an absolute and relative way. Changes at 3, 6, and 12 months in the three groups will be described and compared using the analysis of variance test, or the Kruskal-Wallis test, depending on whether or not the data follow a normal distribution. In all comparisons, a global comparison of the three groups and comparisons between groups by pairing will be carried out (low-dose treatment versus placebo, high-dose treatment versus placebo, high-dose treatment versus low dose, both treatment groups versus placebo). P values will be corrected by Bonferroni test. Regarding handling of missing data, a complete case analysis will be performed if percent of missing data is less than 5%. In another case, a data imputation will be performed for those variables with 25% or less missing values. Variables with more than 25% missing values will be removed from the analysis. The statistical analysis will be carried out by the statistical service of the Jiménez Díaz Foundation University Hospital. Data analyst will be blinded.

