Regenerative medicine is making possible to address unmet therapeutic needs. Specifically, cell-based therapy is positioning itself as one of the most promising approaches, generating great progress and a new frontier in healthcare. Cell therapy programs have opened on a wide range of fields with translational goals, providing sufficient evidence to show that it is a safe treatment [25–27, 43, 44]. Efficacy of the intramuscular administration of autologous Ad-MSC in type 2 DM patients with CLI was demonstrated in the pilot study conducted by Riera et al., showing a statistically significant improvement in health-related quality of life, an increase in ABI, and a decrease in RB category in the post-treatment period [32]. To our knowledge, no randomized clinical trial protocols consisting of the administration of Ad-MSC in type 2 DM patients with CLI have been published to date. Given that current treatment is not established in daily clinical practice, it is essential to promote and systematize the knowledge already obtained with the aim of developing well-designed cell therapy-based clinical trials. In our previous experience, management of the IMP to ensure the viability and survival of MSC is essential and was discussed in multiple meetings, leading to the development of a protocol for the correct handling and administration of the cell-based therapy. The implementation of this protocol implies a great coordination effort, in which basic and clinical researchers worked together to ensure that the living medicinal product reaches from the laboratory to the patient. Finally, the design of a multicenter independent-driven clinical trial based on cell therapy administration represents a challenge requiring a large logistical organization (as shown in Figs. 2 and 3) and great involvement and collaboration from the entire research team for the study to be feasible. “Feasibility” of the NOMA clinical trial also refers to the following characteristics of the proposed intervention: (i) On the one hand, it is an allogeneic product, in which 30 batches of cell therapy at a dose of 1 × 10^6^ cells/kg of weight, and 30 batches of cell therapy at a dose of 2 × 10^6^ cells/kg of body weight are obtained from a single liposuction. In autologous uses, patient needs to undergo liposuction in a first stage, and the administration of the cell therapy in a second stage. (ii) On the other hand, an intramuscular administration has been proposed, technically simpler than intravascular administration. Hence, an easy-to-apply cell therapy is proposed in this protocol, contributing to the feasibility of the intervention in a clinical setting. This will undoubtfully be useful to conduct academic clinical trials in the field of cell therapy in the near future.

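### Bonferroni correction covers the primary safety comparisons, where it makes harm harder to declare, and for efficacy it gives up power that gating on the planned global test would keep

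*Protocol article*

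**What the plan says.** The primary outcome is safety. Under Primary outcome measure: "Safety will be assessed comparing the rate of treatment related complications between groups". Under Statistical analysis: "24 h and 3, 6, and 12 months complication rates will be described and compared for the three groups using the Chi-square test", or Fisher's exact test if needed.

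The same section then says: "In all comparisons, a global comparison of the three groups and comparisons between groups by pairing will be carried out". It lists four contrasts: low dose versus placebo, high dose versus placebo, high versus low dose, and both doses together versus placebo. The correction follows in one sentence: "P values will be corrected by Bonferroni test".

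That sentence makes no exception for safety, does not say how many tests form a family, and gives the global test no role in deciding whether the contrasts are read. The section also plans to describe rates and to give 95% confidence intervals where possible.

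On size, the Sample size calculation section gives 30 per group and says: "A formal size calculation based on the expected differences for the primary outcome has not been performed".

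**The concern.** A multiplicity correction protects against false positive claims. In a safety comparison the costlier error is usually the opposite one, a real excess of complications that goes undeclared. Applying Bonferroni to the primary outcome moves the threshold in the wrong direction, in arms of only 30.

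For efficacy the question is efficiency. The plan already pays for a global test on each outcome. In a three-arm trial that test, used as a gate, is enough to protect the contrasts that follow it. Correcting the contrasts by Bonferroni instead costs power in a dose-finding trial that has no power calculation behind it.

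**Working it through.** **Inputs.** From the protocol article: 30 per arm, three arms, four contrasts, four time points for safety. Assumed, because the article gives no figure: two-sided alpha 0.05 (in line with the 95% intervals), the complication rates, and the standardised efficacy effect. There is no stated power to reproduce.

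**Step 1: threshold.** Bonferroni over the four listed contrasts gives 0.05/4 = 0.0125 per contrast. The article does not fix the family. If the four time points were included, it would be 0.05/16 = 0.0031. The main figures below use four.

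**Step 2: safety power.** Power is the sum, over all pairs of event counts in 30 and 30, of the binomial probabilities of the pairs whose two-sided Fisher p value is at or below the threshold.

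| Placebo vs active (assumed) | 0.05 | 0.0125 | 0.0031 (16-test reading) |
|---|---|---|---|
| 10% vs 30% | 37% | 21% | 9% |
| 5% vs 25% | 44% | 28% | 11% |
| 10% vs 40% | 70% | 49% | 30% |

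In events: with 3/30 on placebo, an active arm needs 11 complications to be significant at 0.05 and 13 at 0.0125. With 2/30 it needs 9 and 11.

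**Step 3: why the gate suffices.** Write P, L, H for the three group parameters. The four nulls are L = P, H = P, H = L and (L + H)/2 = P. Any two of them force all three to be equal; for example, L = P with (L + H)/2 = P gives H = P. So either all three groups are equal, and the 5% global test limits the error, or at most one null is true, and its own 5% test limits the error. That is closed testing, and it holds within one outcome and one time point.

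**Step 4: efficacy power, continuous outcome.** Simulation of 200,000 trials, 30 per arm, pooled-variance contrasts; high dose versus placebo:

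| Means in SD (placebo, low, high) | Bonferroni over four | Gated on global test |
|---|---|---|
| 0, 0, 0.75 | 64% | 78% |
| 0, 0.375, 0.75 | 64% | 72% |
| 0, 0.75, 0.75 | 64% | 78% |

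Gated familywise error was 5.0% within simulation error wherever a null was true. Under the global null, Bonferroni used only 3.5%.

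**Step 5: the gate loses nothing here.** A contrast with p at or below 0.0125 on 87 degrees of freedom has |t| of at least 2.55. Since F is at least t²/2, F is at least 2.55²/2 = 3.25, above the 5% critical value of 3.10. For ANOVA contrasts, whatever Bonferroni over four rejects, the gated rule also rejects.

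**Step 6: binary efficacy outcomes.** Exact enumeration at 10% on placebo and 40% on high dose: Fisher pairings go from 49% under Bonferroni to 67–70% gated, and Chi-square pairings from 61% to 70–77%, depending on the low-dose rate. Gated familywise error reached 5.3% with Chi-square pairings, because of the approximation, and at most 4.6% with Fisher pairings.

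**Step 7: precision.** With 0/30 events, the exact two-sided 95% upper limit is 1 − 0.025^(1/30) = 11.6%. The risk-difference half-width is 1.96·√[(p₁(1−p₁) + p₂(1−p₂))/30]:
- 10% vs 10%: 15 points
- 10% vs 30%: 20 points
- 30% vs 30%: 1.96·√(0.42/30) = 23 points

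**The case against.** The strongest reply is that Bonferroni is valid and conservative, and that most of the insensitivity to harm is not its doing. That second part stands. At 10% versus 30% the power is only 37% with no correction at all, so a threefold rise would more often be missed than found either way; the correction takes a further 16 points. A reader might infer that the plan hides harm, or that it will present a non-significant result as proof of safety. The document supports neither. Complication rates will be described by group with 95% intervals where possible, Bonferroni does not alter those, and nowhere is a non-significant result equated with safety.

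The efficacy gain also depends on the dose pattern. For a graded response it is 8 points, not 14, and the chance of at least one significant contrast moves only from 68% to 73%; with both doses at 0.75 SD it moves from 82% to 85%. A claim that real dose effects would generally be discarded is too strong.

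The 16-test powers apply under one possible reading of an undefined family. If that reading were intended, the gate would give up control across time points that Bonferroni was meant to supply.

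It is tempting to add that sizing by "A sample size of 30 patients per group was deemed appropriated based on the possibility to reach normality" is a weak reason for a binary primary outcome, and that "no previous data on the preliminary efficacy of Ad-MSC with CLI including type 2 DM patients are available to date" sits badly with the Discussion's "Efficacy of the intramuscular administration of autologous Ad-MSC in type 2 DM patients with CLI was demonstrated in the pilot study". Both are wording matters. The quantitative secondary outcomes give normality some relevance, the pilot was autologous, and neither remark changes a result here.

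**Conclusion.** The point holds in a limited form. The correction as written reaches the primary safety contrasts, and there it raises the bar for declaring harm: from 37% to 21% power at 10% versus 30%, and from 44% to 28% at 5% versus 25%. Whether the global safety p value is also corrected is unclear; the contrasts are on any reading. The arm size is the larger limit, and the planned description of rates softens the effect.

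For efficacy, replacing Bonferroni over the four contrasts by the gate raises high-dose versus placebo power from 64% to 72–78% at 0.75 SD, with familywise error held at 5% within one outcome and time point. For ANOVA contrasts this is a strict gain rather than a matter of taste. All power figures rest on assumed rates, effects and a two-sided 5% level. The change is worth making, but the trial does not stand or fall by it.

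**What to change.** **Safety.** State that safety comparisons are not adjusted for multiplicity. Report each arm's complication proportion with its 95% interval, and the risk difference versus placebo for each dose and for both doses pooled, with 95% intervals. Add that a non-significant difference is not evidence of safety.

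**Efficacy.** Replace Bonferroni over the contrasts by this rule: test the three groups globally at 5%; only if that is significant, test each of the four contrasts at 5%. For sparse binary outcomes use Fisher pairings, since Chi-square pairings can slightly exceed 5%. State that control applies within one outcome and time point.

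**Precision, if quoted.** With 0/30 events the 95% upper limit is 11.6%; the half-width of a risk difference is about 15 to 23 points at event rates of 10–30%.

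**Cost.** Wording only; no change to data collection or sample size. Isolated safety false alarms become more likely and must be labelled descriptive. The gate gives no protection across time points or outcomes; if that is wanted, it needs its own rule.

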**Methods:**

A multicenter, randomized double-blind, placebo-controlled trial has been designed. Ninety eligible patients will be randomly assigned at a ratio 1:1:1 to one of the following: control group (*n* = 30), low-cell dose treatment group (*n* = 30), and high-cell dose treatment group (*n* = 30). Treatment will be administered in a single-dose way and patients will be followed for 12 months. Primary outcome (safety) will be evaluated by measuring the rate of adverse events within the study period. Secondary outcomes (efficacy) will be measured by assessing clinical, analytical, and imaging-test parameters. Tertiary outcome (quality of life) will be evaluated with SF-12 and VascuQol-6 scales.

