## Background

Critical lower limb ischemia (CLI) is characterized by chronic pain at rest, ulcers or gangrene attributable to a proven occlusive arterial disease [1]. The evolution of CLI, in the context of a generalized atherosclerotic disease, implies high morbidity and mortality. CLI develops earlier and with greater intensity in patients with diabetes mellitus, with complications that may result in the amputation of the limb and even death [2, 3]. A public health goal of the standard of care is to decrease global cardiovascular risk through the control of risk factors by changes on lifestyle habits (quitting smoking, healthy diet, physical exercise) and pharmacological treatment (antiplatelet therapy, statins) [4]. However, there is insufficient evidence to show that this approach improves substantially the course of this disease [5]. Surgical or endovascular revascularization is often the treatment of choice, despite the fact that it is an invasive procedure that carries a high rate of complications. In addition, the health cost of this pathology is quite high. The treatment of the diabetic foot, and specifically critical limb ischemia, is the second most expensive complication in economic terms for the health system, just behind dialysis [6]. Efforts to prevent loss of the affected limb also include soft tissue debridement, minor amputations, and even skin grafts, all of which are costly procedures. In this context, given the high number of amputations that are still practiced annually worldwide, we are still in need of a cost-effective and easy-to-apply treatment [7]. Recently, research has shown that it is possible to improve tissue perfusion through therapeutic angiogenesis, making it one of the most promising strategies used to promote the proliferation of collateral vessels in ischemic tissues. In this sense, there are several methods to improve tissue perfusion, such as the administration of recombinant growth factors [8–11], or the constitutive expression of genes that encode for these factors through gene therapy [12]. Although both therapies have shown to promote angiogenesis in ischemic conditions in preclinical models [13], modest results were obtained when clinically applied [14–17]. In contrast, it has been shown both in animal models and in humans that cell therapy can induce therapeutic angiogenesis [18–20]. Cell-based therapies aiming to promote vascular regeneration gained interest with the discovery of a subpopulation of vasculogenic endothelial progenitor cells as reported by Asahara et al [17]. Human endothelial cell progenitors were isolated from peripheral blood by magnetic bead selection based on cell surface antigen expression. In animal models of ischemia, these cells have the ability to colonize the site of injury of ischemic tissue and secrete a number of vascular growth factors that can lead to clinically effective neovascularization [17]. It seems that these cells contribute to angiogenesis through the secretion of angiogenic cytokines and proteases such as matrix metalloproteases (MMPs), among others, helping the stability and growth of the endothelial and vascular network [21]. In 2002, the pioneering results of the TACT study (Therapeutic Angiogenesis using Cell Transplantation study) were published, consisting of a pilot uncontrolled safety study (*n* = 25) and a randomized controlled clinical trial to evaluate the use of mononuclear cells of bone marrow (BM) by intramuscular injection in 22 patients for treat peripheral arterial disease (PAD). Cell therapy with BM-derived mononuclear cells significantly improved ABI (difference 0.09 [95% CI 0.06–0.11]), transcutaneous oxygen pressure (pTcO2), (13 [9–17]), rest pain (− 0.85 [− 1.6 to − 0.12]) and pain-free walking time (1.2 [0.7–1.7]) in all treated patients [22]. Unfortunately, those with poorly controlled diabetes were excluded from the trial. As the prevalence of PAD increases in patients with type 2 diabetes mellitus (type 2 DM) it is logical to assume that this population group is a potential candidate for cell therapy [22]. Since then, several studies have been carried out in which the transplantation of the mononuclear fraction of BM or peripheral blood has been shown to improve the endothelial function in the territories in which they were administered [23] and to improve ischemic pain and the healing of ulcers [24]. In a phase I/II, open-label, non-comparative clinical trial, safety and feasibility of treatment with autologous mesenchymal stromal cells (MSC) derived from BM and administered intra-arterially in patients with type 2 DM and lower limb ischemia was studied. All of the participants (*n* = 20) showed an increase in leg vascularization demonstrated by angiography and 100% of the ulcers healed. During the first year of follow-up, 7 minor amputations were performed, but no patient suffered a major amputation [25]. Cañizo et al. reported the first case of a patient with CLI treated with peripheral blood CD133+ cells. There were no major amputations and after 17 months of follow-up, patients experienced symptomatic and functional improvement. The group also observed the appearance of blood flow in the posterior tibial artery that was absent before the procedure [26]. The search for the most appropriate cell type for this pathology remains a challenge today [27], but the use of MSC is gaining prominence. The fact that these cells have trophic, immunomodulatory, and anti-inflammatory properties and liposuction is an easy and minimally invasive technique places them as suitable candidates for clinical use. The study that we propose here focuses on the development and optimization of an advanced therapy medicinal product (ATMP) based on adipose tissue-derived MSC (Ad-MSC) to be administered intramuscularly to patients with type 2 DM and CLI within a multicenter randomized phase II clinical trial, favoring the translation of this cellular therapy to clinical practice. If proven safe and effective, an accessible, easy and minimally invasive treatment will be available for patients without any other option or that can even be associated with existing surgical treatments and improve their results.

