### Recruitment of eligible participants

Patients will be recruited by the attending clinicians (vascular surgeons) among the population of chronic, type 2 DM patients with peripheral arteriopathy that is usually under periodic follow-up in the outpatient clinic. Proposal to participate in the clinical trial will take place in one of these routine outpatient visits. Clinicians will explain to each subject the nature of the study, its purposes, procedures, expected duration, and the potential risks and benefits related to participation in the trial, as well as any inconvenience that this may entail. Patients will have enough time to read and understand the explanations before dating and signing the informed consent and will receive a copy of the signed document. Eligible patients will be (1) those aged between 40 and 90 years; (2) with type 2 DM diagnosed for more than one year; (3) with severe vascular arteriosclerosis, defined as Rutherford-Becker (RB) category 4 and 5 [23], mono or bilateral; and (4) with impossibility of surgical or endovascular revascularization or failure of revascularization surgery performed, at least 30 days before inclusion in the study. Patients with CLI and tissue loss in the target limb (RB category 6) or previous major amputation in the target limb will be excluded from the trial. Detailed eligibility criteria are described in ClinicalTrials.gov (NCT04466007). During trial conduct, periodic contacts with investigators and a trial newsletter are foreseen to assess possible difficulties in recruitment in advance and to keep investigator team informed of recruitment evolution. No specific methods to minimize attrition are foreseen. Eligible patients are severely ill patients that are usually adherent to medical visits, and thus a high drop-out rate is not expected.

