#### Secondary outcome measures

Efficacy will be assessed through the following variables:

(a) Vascularity in the target limb will be assessed through mean change in percentage of vascular flow measured by MRI in the target limb at 12 months from baseline between groups. MRI will be centrally read by a blinded radiologist. (b) Disease severity will be evaluated through percentage of patients with an improvement in RB category at 3, 6, and 12 months from baseline [33] between groups. This scale is usually used in patients with chronic arterial disease to classify chronic arterial disease into clinical categories (category 0, asymptomatic; category 1, mild claudication; category 2, moderate claudication; category 3, severe claudication; category 4, pain at rest; category 5, minor tissue loss; category 6, ulcer o gangrene). (c) Ulcer healing (if any) will be assessed through the percentage of patients with a decrease in SVS-“WIfI” wound classification [34, 35] at 3, 6, and 12 months from baseline between groups. SVS-WIfI classification aims to be as functional in diagnosing PAD as the tumor-node-metastasis-based diagnosis system (TNM). Three measurable parameters are collected: wound (extension and depth), ischemia (blood flow), and foot infection (presence and extension). (d) PAD evolution will be evaluated by % of patients with an increase in ankle-brachial index at 3, 6, and 12 months from baseline between groups [36]. (e) Pain intensity will be assessed through mean change in visual analogue scale (VAS) from 0 to 10 cm, as described by the patient (0, absence of pain; 1–3, mild; 4–7, moderate; 8–10, severe) and percentage of patients with an improvement in pain intensity at rest at 3, 6, and 12 months from baseline between groups. (f) Percentage of patients with a decrease in temperature (°C), increase in gastrocnemius muscle perimeter (cm) and decrease in neuropathic symptoms of the treated limb compared with contralateral at 3, 6, and 12 months from baseline. (g) Mean change in percentage of amputations in each group at the end of the study will be registered.

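### The rule that removes any outcome with more than 25% missing values lets events after randomisation decide which outcomes are reported, and it makes no distinction for death or loss of the target limb

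*Protocol article*

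**What the plan says.** The Statistical analysis section of the protocol article sets one rule in three bands, driven only by the share of values missing:

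- Low band: "a complete case analysis will be performed if percent of missing data is less than 5" per cent.
- Middle band: otherwise, "a data imputation will be performed for those variables with 25% or less missing values". The imputation method is not named.
- High band: "Variables with more than 25% missing values will be removed from the analysis".

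The same section covers primary, secondary and tertiary outcomes, and the rule exempts none of them.

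Three other places bear on it. The Background describes the disease as having "complications that may result in the amputation of the limb and even death". Recruitment of eligible participants says that patients usually keep their visits, "thus a high drop-out rate is not expected", without giving a figure or mentioning death or limb loss. Secondary outcome measures lists MRI flow in the target limb, ankle-brachial index, calf (gastrocnemius) perimeter and limb temperature, all of which need a limb to measure. It also lists amputations as a separate outcome.

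**The concern.** Two things are wrong with a rule that looks only at the share missing.

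First, the high band deletes a pre-specified outcome on the basis of data seen after randomisation. In this population part of the missingness may itself be a bad outcome, because a patient who dies or loses the target limb has no later MRI flow, ankle-brachial index, calf perimeter or temperature in that limb. Enough poor results could then remove the outcome that would have shown them.

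Second, the middle band fills such values in without distinction. If the imputation borrows from patients who kept the limb, it gives a plausible value to a limb that no longer exists. An arm with more limb loss can then look better on the limb measures than it was.

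**Working it through.** **Inputs.** From the documents: cut-offs of 5% and 25%; 90 patients in three arms of 30 ("Ninety eligible patients will be randomly assigned at a ratio 1:1:1"). The document gives no rate of death, amputation or drop-out for this trial, and for the sample size "A formal size calculation based on the expected differences for the primary outcome has not been performed", so there is no planned figure to reproduce. All rates below are assumptions, shown as a range. The counts assume that all 90 patients are in the analysed population.

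**Step 1: cut-offs as patient counts.**
- 22/90 = 24.4% and 23/90 = 25.6%, so removal starts at 23 missing.
- 4/90 = 4.4% and 5/90 = 5.6%, so complete case applies to at most 4 missing.
- From 5 to 22 missing, values are imputed.

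**Step 2: chance that an outcome is removed.** This is P(X ≥ 23) with X binomial (90, p).

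| True missingness p | P(removed) |
|---|---|
| 10% | about 0 |
| 15% | 0.006 |
| 20% | 0.12 |
| 25% | 0.49 |
| 30% | 0.85 |
| 35% | 0.98 |

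**Step 3: what could produce such missingness.** With independent death d, major amputation a and other loss o, the share missing for a limb measure is 1 − (1 − d)(1 − a)(1 − o).
- 5%, 10%, 5%: 1 − 0.95 × 0.90 × 0.95 = 18.8%, P(removed) = 0.07.
- 10%, 15%, 5%: 1 − 0.90 × 0.85 × 0.95 = 27.3%, P(removed) = 0.69.
- 15%, 20%, 5%: 1 − 0.85 × 0.80 × 0.95 = 35.4%, P(removed) = 0.98.

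**Step 4: bias in the imputation band.** Take two arms of 30 with 9 true responders each, and 9 versus 3 patients lost to death or amputation, none of them responders. These 12 losses are 12/90 = 13.3% of the trial. With 0 to 10 more in the third arm the total is 13.3% to 24.4%, so imputation applies.
- Lost patients counted as not improved: 9/30 = 30% versus 9/30 = 30%.
- Imputed at the response rate of those measured: (9 + 9 × 9/21)/30 = 42.9% versus (9 + 3 × 9/27)/30 = 33.3%.
- The spurious advantage is 42.9 − 33.3 = 9.6 points for the arm with more loss.
- A milder case, 6 versus 3 lost: 9/24 = 37.5% versus 9/27 = 33.3%, or 4.2 points.

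For a continuous outcome with no true effect and the worst patients in each arm lost (simulation, 30 per arm, 4000 runs), leaving them out shifts the comparison toward the higher-loss arm by about 0.30 SD at 30% versus 10% loss and 0.16 SD at 20% versus 10%. At 10% versus 10% the shift is about zero.

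**The case against.** Several stronger readings are tempting, and the documents do not support them.

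- **That the plan declares death and limb loss to be ordinary missing data.** It does not mention them in the missing-data rule. The fair statement is that it makes no distinction. The full protocol or the analysis plan, neither shown, may add one.
- **That complete-case analysis hides large differences in limb loss.** It cannot, because it applies only up to 4 missing of 90. Even with all 4 in one arm and 40% improving among the 26 measured, the figure over 30 is 0.40 × 26/30 = 34.7%, a shift of about 5 points.
- **That limb loss always flatters an arm.** The bias needs unequal loss, with the poorer patients lost.
- **That ulcer healing would be deleted because patients with rest pain only have no ulcer.** The outcome is worded "Ulcer healing (if any) will be assessed through the percentage of patients with a decrease", and the parenthesis most naturally limits it to patients who have an ulcer. The others are then not applicable rather than missing. Only the denominator needs stating.

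Other points for the plan also stand. Limb loss is not concealed, since amputations are recorded and reported as their own outcome. At 15% missingness or less, deletion is very unlikely. The authors expect little drop-out, exclude the most severe Rutherford-Becker category, and cite in the Background a study of 20 patients with no major amputation in the first year, although it was uncontrolled and used a different cell product. The primary outcome, treatment-related complications, does not need a surviving limb.

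What this does not answer is the removal sentence itself. It is a stated rule, and a separate analysis plan could repair it only by contradicting it. A separate amputation count does not correct the limb measures either.

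**Conclusion.** The point holds for the 25% removal rule and, conditionally, for the imputation band. The plan lets the number of missing values after randomisation decide whether a pre-specified outcome is reported. The probability of that runs from under 1% at 15% missingness to 85% at 30%, and the documents give no basis for choosing within that range. The bias from imputing lost limbs is about 4 to 10 points in the responder examples with unequal loss, and about zero with equal loss. It assumes imputation from survivors, since the method is not named.

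This should be fixed but is not critical: the limb measures at risk are secondary outcomes in a trial without a formal sample size calculation.

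**What to change.** 1. Delete the sentence that removes variables above 25% missing. Report every pre-specified outcome with its share missing by arm, using multiple imputation or a mixed model whatever that share, plus a sensitivity analysis.
2. For the limb outcomes expressed as a percentage improved, count death or major amputation of the target limb before the visit as not improved, within the plan's own analysis population, instead of imputing a value.
3. State that the denominator for ulcer healing is patients with an ulcer at baseline.

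Worst-rank scoring of quantitative limb measures is one defensible option among several and is not required here.

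The cost is analysis wording and a little more analysis work, with no change to visits, treatment or data collection. Improvement percentages become slightly less favourable. The change should be made before unblinding, because it decides which outcomes are reported.
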